#### Core biopsies

Biopsy samples will be collected as standard using a 14G core biopsy needle under ultrasound guidance in the Department of Radiology at Belfast City Hospital. Two core biopsies will be sharply dissected into at least four smaller samples (approximately 5 mm^3^ each) and placed in individual Eppendorf tubes, then snap-frozen with liquid nitrogen and stored for later use. Two core biopsies will be placed in individual formalin-containing sample pots, after which they will be formalin-fixed paraffin-embedded (FFPE) as per standard operating procedures within the Belfast Trust.

Core biopsies will be taken on day 1 (baseline), day 84 (±3 days following the end of the first arm) and day 196 (±3 days following the end of the second arm).

#### Histopathological analysis

One FFPE sample will be assessed by a histopathologist to ensure adequate sampling of glandular tissue.

#### Comet assays

Two frozen biopsy specimens will be used to perform tissue-based comet assays to assess DNA damage.

#### Immunohistochemistry

One FFPE core biopsy sample will be sectioned and stained with antibodies against 53BP1 and phosphorylated histone A2 variant X (γH2AX) using conventional and fluorescent immunohistochemistry to assess DNA DSBs in these samples.

Additional sections will also be stained for RANK and RANKL as well as Ki67 using immunohistochemistry.

#### Mass spectrometry

Two frozen biopsy specimens will be used to examine concentrations of oestrogen metabolites 2-hydroxyestradiol (2-OHE_2_) and 4-hydroxyestradiol (4-OHE_2_), using ultra performance liquid chromatography tandem mass spectrometry (UPLC-MS/MS).

#### Serum samples

Serum sampling will be performed on day 1 (baseline), day 84 (±3 days following the end of the first arm) and day 196 (± days following, end of the second arm). Participants will undergo venepuncture with blood samples collected in two silica (clot activator) coated 10 mL blood sample tubes. After the minimum recommended clotting time (60 min), blood samples will be centrifuged to allow separation of serum from blood cells, with the serum stored at −80°C in 1 mL aliquots in RNAse free tubes. Following sample accrual, samples will be thawed and serum 2-OHE_2_ and 4-OHE_2_ levels, and levels of depurinating DNA adducts (common types of DNA damage caused by oestrogen metabolites) will be measured using UPLC-MS/MS.

#### Urine samples

Urine sampling will be performed on day 1 (baseline), day 84 (±3 days following, end of the first arm) and day 196 (±3 days following, end of the second arm). Mid-stream urine samples will be collected in sterile containers. Within 2 hours of collection samples will be centrifuged to separate debris from the urine and then stored at −80°C in 500 µL aliquots in RNAse free tubes. Following sample accrual. Samples will be thawed and urinary 2-OHE_2_ and 4-OHE_2_ levels and levels of depurinating DNA adducts will be measured using UPLC-MS/MS.

#### Whole blood sampling

Each participant will provide one whole blood sample at one time point in the study. This will be performed at baseline (day 1), unless the patient is already enrolled and receiving treatment, in which case the whole blood sampling will be performed at the end of the treatment arm that they are currently receiving (day 84±3 days or day 196±3 days).

The whole blood samples will be collected at the same venepuncture session as serum sampling. Blood will be collected into one EDTA-coated tube and frozen/stored at −80°C in 1 mL aliquots. Samples will be retained for future use including DNA extraction.

The timeframe for interventions and assessments is summarised in table 3.

**Table 3 T3:** Summary of assessments and interventions

Time point	<30 days prior to entry	Week 1	Week 4	Week 8	Week 12	Week 16	Week 20	Week 24	Week 28	Week 32 (end of trial)
Enrolment										
Informed consent	A+B									
Baseline history	A+B									
Eligibility screen and pregnancy test		A+B				A+B				
Treatment allocation		A+B								
Conmeds	A+B	A+B	A	A	A+B	A+B	B	B	A+B	A+B
Interventions										
Start tamoxifen (12 weeks)		B				A				
Start anastrozole (12 weeks)		A				B				
Goserelin implant injection		A	A	A		B	B	B		
Assessments										
Quality of life assessment		A+B			A+B				A+B	
Core breast biopsies ×3		A+B			A+B				A+B	
Blood samples for oestrogen and metabolite levels		A+B			A+B				A+B	
Blood sample for whole blood		A+B			A+B				A+B	
Urine samples for oestrogen and metabolite levels		A+B			A+B				A+B	
Adverse event assessment	A+B	A+B			A+B	A+B			A+B	A+B

A corresponds to treatment arm A of the study (goserelin and anastrozole followed by tamoxifen. B corresponds to treatment arm B, tamixofen followed by goserelin and anastrozole.

### Comparisons

Each participant acts as her own control. The results from each individual’s set of samples (core biopsies, serum and urine) and questionnaires, taken at baseline, end of the first arm and end of the second arm will be compared. The results will not be compared between patients.

### Statistical analysis

This study is primarily aimed to determine acceptability and tolerability of the proposed chemopreventive treatments. Therefore, no formal sample size calculation has been carried out, as the laboratory endpoints are all exploratory.

For these reasons, no formal statistical analysis is planned. Nonetheless, descriptive statistics will be used to summarise the principal and experimental findings of the study.

### Laboratory analysis

The proposed translational studies include performing comet assays on fresh-frozen breast core biopsies at baseline and after each treatment arm. The comet assay protocol has been optimised on breast cell cultures as well as fresh-frozen breast biopsy samples using neutral lysis techniques with automated scoring performed on a high content screening system. FFPE breast core biopsy blocks are created at the same time points as fresh-frozen samples. Formation of γH2AX in response to DNA DSBs provides the basis for a sensitive immunohistochemical assay of DNA damage in human biopsies and has been optimised in FFPE breast samples with simultaneous staining for 53BP1, which localises to DNA strand breaks, with foci numbers proportional to DNA damage levels. Based on our hypothesis, the anticipated decrease in measurable DNA damage in response to oestrogen suppression would support the use of this strategy as a chemoprevention option in BRCA1 mutation carriers.

Further FFPE sections will be analysed for Ki67, RANK and RANKL expression to assess the effect of treatment on these markers of proliferation (Ki67) and progesterone signalling (RANK/RANKL). As the LHRHa used to suppress oestrogen will also result in progesterone suppression, it is expected that RANK and RANKL expression will also decrease. Given that inhibition of RANK has been shown to reduce breast cell proliferation in BRCA1 mutation carriers, it is possible that LHRHa treatment might be an alternative way of downregulating this pathway and potentially decreasing the development of highly proliferative cells with grossly aberrant DNA repair observed in BRCA1 precancerous tissues with high levels of RANK/RANKL expression.^15^

Oestrogen metabolite levels in serum and urine will be measured using UPLC-MS/MS and have been optimised on healthy volunteer samples with permission from Queen’s University Ethics Committee.

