## Abstract

**Introduction:**

BRCA1 mutation carriers have a significant lifetime risk of breast cancer, with their primary risk-reduction option being bilateral mastectomy. Preclinical work from our laboratory demonstrated that in BRCA1-deficient breast cells, oestrogen and its metabolites are capable of driving DNA damage and subsequent genomic instability, which are well-defined early events in BRCA1-related cancers. Based on this, we hypothesise that a chemopreventive approach which reduces circulating oestrogen levels may reduce DNA damage and genomic instability, thereby providing an alternative to risk-reducing surgery.

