**Methods and analysis:**

12 premenopausal women with pathogenic BRCA1 mutations and no previous risk-reducing surgery will be recruited from family history clinics. Participants will be allocated 1:1 to two arms. All will undergo baseline breast biopsies, blood and urine sampling, and quality of life questionnaires. Group A will receive goserelin 3.6 mg/28 days by subcutaneous injection, plus oral anastrozole 1 mg/day, for 12 weeks. Group B will receive oral tamoxifen 20 mg/day for 12 weeks. Following treatment, both groups will provide repeat biopsies, blood and urine samples, and questionnaires. Following a 1-month washout period, the groups will cross over, group A receiving tamoxifen and group B goserelin and anastrozole for a further 12 weeks. After treatment, biopsies, blood and urine samples, and questionnaires will be repeated. DNA damage will be assessed in core biopsies, while blood and urine samples will be used to measure oestrogen metabolite and DNA adduct levels.

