Taken with evidence from clinical trials, which demonstrate no benefit from SERMs in reducing the incidence of ER-negative tumours, this suggests that SERMs are unlikely to be effective chemopreventive agents in BRCA1 mutation carriers (who are more likely to develop ER-negative tumours). Our data suggest that a chemopreventive approach which lowers circulating oestrogen levels and reduces exposure to oestrogen metabolites within the breast tissue may be more successful by removing this driver of genomic instability. While DNA damage is not at present a validated biomarker of cancer risk in mutation carriers, as described earlier, genomic instability is a well-characterised early hallmark of BRCA1-associated breast tumours. Consistent with this, mice harbouring specific point mutations within BRCA1 affecting its DNA repair function while conserving other protein functions (E3 ligase, transcriptional activity and so on) develop tumours.^20^ This supports the link between DNA damage, genomic instability and tumourigenesis in BRCA1-deficient breast cells.

In postmenopausal women (or premenopausal women who have undergone oophorectomy), the use of an AI may be considered. In premenopausal women with intact ovaries, the induction of reversible ovarian suppression using a luteinising hormone releasing hormone agonist (LHRHa) in combination with an AI, to suppress subsequent aromatase-mediated oestrogen production, may be effective.

Progesterone signalling has also recently been implicated in BRCA1-related tumourigenesis, with the tumour necrosis factor superfamily member RANK (receptor activator of nuclear factor κ B) and its corresponding ligand RANKL (ligand of receptor activator of nuclear factor κ B) functioning as key factors in this pathway and potential targets for chemoprevention.^21^ Importantly, LHRHa suppression of the hypothalamic-pituitary axis will also result in decreased progesterone levels, which will consequently reduce progesterone-dependent RANK/RANKL signalling. Additionally, expression of the progesterone receptor (PR), a critical mediator of the progesterone/RANK/RANKL pathway, is itself driven by oestrogen signalling through the ER. Taken together, the suppression of oestrogen is likely to provide chemopreventive potential, similar to or surpassing that demonstrated through RANK/RANKL suppression.

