**Figure 1 F1:**
[figure not shown]
Chemoprevention in BRCA1 mutation carriers (CIBRAC) trial schema.

The crossover design allows comparison of outcomes from both treatments with the participant baseline; thus, each participant acts as their own control for both treatment arms. Blinding or masking is not achievable given the nature of administration of goserelin (subcutaneous implant). Given that each participant will receive both treatments without blinding, randomisation was felt unnecessary, and alternate allocation of treatment groups in order of recruitment is adequate. The setting of the trial in tertiary care (family history breast clinics) reflects the main location for the ongoing care and management of this cohort.

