### Trial registration

CIBRAC is registered as a clinical trial of an interventional medicinal product on the European Clinical Trials Database, as EudraCT: 2016-001087-11. Trial registration data are provided in table 5.

**Table 5 T5:** Trial registration data

Data category	Information
Primary registry and trial registration number	EudraCT: 2016-001087-11
Date of registration in primary registry	9 March 2016
Sources of monetary or material support	Supported by a Cancer Research UK Clinical Research Training Fellowship
Sponsor	Belfast Health and Social Care Trust
Contact for public queries	[name] ([contact])
Contact for scientific queries	[name] ([contact]), [name] ([contact])
Public title	CIBRAC: chemoprevention in BRCA1 mutation carriers
Scientific title	Chemoprevention in BRCA1 mutation carriers (CIBRAC): an open allocation crossover trial assessing mechanisms of chemoprevention of goserelin and anastrozole versus tamoxifen
Countries of recruitment	UK (Northern Ireland)
Interventions	Tamoxifen 20 mg daily (oral), goserelin 3.6 mg every 28 days (subcutaneously) plus anastrozole 1 mg daily (oral)
Key inclusion criteria	Ages eligible for study ≥18 years. Sex eligible for study: female. Known pathogenic germline BRCA1 mutation. Premenopausal. No previous breast or ovarian risk-reducing surgery.
Key exclusion criteria	Personal history of breast or ovarian carcinoma. Previous risk-reducing breast or ovarian surgery. Postmenopausal status.
Study type	Interventional. Allocation: alternate treatment allocation, non-randomised, non-blinded. Primary purpose: prevention. Phase II.
Date of first enrolment	May 2017
Recruitment status	Recruiting
Primary outcome	Establish the acceptability of trial treatments as a chemopreventive strategy in BRCA1 mutation carriers, as measured by the number of patients entering the trial and compliance with treatment.
Key secondary outcomes	To establish tolerability of trial treatments and procedures.

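### Support for oestrogen suppression is tied to the fall in DNA damage on goserelin/anastrozole alone, and the contrast with tamoxifen is given no part in the conclusion

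*Protocol article*

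**What the plan says.** The Introduction sets out an expectation about both treatments. On tamoxifen's class, "this suggests that SERMs are unlikely to be effective chemopreventive agents in BRCA1 mutation carriers". On the alternative, an approach that "lowers circulating oestrogen levels and reduces exposure to oestrogen metabolites within the breast tissue may be more successful". The scientific title in Table 5 describes the trial as "assessing mechanisms of chemoprevention of goserelin and anastrozole versus tamoxifen", and the Patient and public involvement section calls the comparator an active control.

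The sentence labelled as the hypothesis, in the Abstract, is narrower and does not mention tamoxifen: "we hypothesise that a chemopreventive approach which reduces circulating oestrogen levels may reduce DNA damage and genomic instability".

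The inference is stated under Laboratory analysis: "the anticipated decrease in measurable DNA damage in response to oestrogen suppression would support the use of this strategy as a chemoprevention option". The Design section frames the contrast in the same one-drug-at-a-time way: "The crossover design allows comparison of outcomes from both treatments with the participant baseline". The Comparisons section says that each woman's results at baseline and at the end of each treatment course will be compared with one another. The Statistical analysis section plans descriptive statistics only and calls the laboratory endpoints exploratory.

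**The concern.** The argument for this regimen in BRCA1 carriers is that it removes a driver of genomic instability that a SERM leaves in place. Each woman receives both treatments and is biopsied after each, so the trial holds a within-woman comparison that bears directly on that argument. The inference as written does not call on it: it is met whenever damage falls on goserelin/anastrozole, including when damage falls just as much on tamoxifen.

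At stake is what a fall from baseline may be credited to. There is one pre-treatment biopsy, on day 1, and later biopsies on days 84 and 196. Time in the trial, repeat biopsy of the same breast, or an antiproliferative effect common to both drugs could each lower measured damage after day 1. Change from baseline on one treatment cannot separate these from oestrogen lowering. The difference between the two courses, averaged over the two sequences, removes a time effect common to both sequences and any effect common to both drugs.

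**Working it through.** **Inputs**
- n = 12 women, allocated 1:1 to two sequences, each receiving both treatments (Abstract: "12 premenopausal women with pathogenic BRCA1 mutations and no previous risk-reducing surgery will be recruited from family history clinics").
- The criterion for support is a decrease in DNA damage on oestrogen suppression (Laboratory analysis). No threshold, alpha, SD or effect size is given, so there is no figure in the plan to reproduce.
- Assumption: the true fall from baseline is the same on both drugs and equals d standard deviations of within-woman change. The values d = 0.25, 0.5 and 1 are illustrative and do not come from the protocol.

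**The wording side by side**
1. Introduction: a SERM is not expected to work, and oestrogen lowering may do better. This concerns a difference between treatments.
2. Laboratory analysis: damage falls on oestrogen suppression, therefore support. This concerns one treatment.
3. Comparisons: all three time points are compared within each woman. The difference between drugs can be formed, but no section attaches a reading to it.

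If damage falls equally on both drugs, item 2 is satisfied while item 1 gains no support.

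**How often that happens.** The document fixes no threshold, so two criteria are shown, each applied to both contrasts.

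*Criterion 1, direction of the mean only.* For change from baseline, P(mean decrease) = Φ(d√12), with √12 = 3.464:
- d = 0.25: Φ(0.866) = 0.807
- d = 0.5: Φ(1.732) = 0.958
- d = 1: Φ(3.464) = 0.9997

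The drug difference has expectation 0 whatever d is, so it favours goserelin/anastrozole with probability Φ(0) = 0.50.

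*Criterion 2, one-sided 95% t bound excludes zero.* With 11 degrees of freedom the critical value is 1.796. For change from baseline the probability is P(T > 1.796), where T is noncentral t with 11 degrees of freedom and noncentrality d√12. For the drug difference it is 5% by construction, treating the 12 differences as a single sample.

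| Assumed equal fall d | Baseline, direction only | Drug contrast, direction only | Baseline, t bound | Drug contrast, t bound |
|---|---|---|---|---|
| 0.25 | 81% | 50% | 20% | 5% |
| 0.5 | 96% | 50% | 49% | 5% |
| 1 | >99.9% | 50% | 94% | 5% |

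Under either criterion, change from baseline gives support more often than the drug contrast at every assumed d, although in each case the regimen does no better than tamoxifen.

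**The case against.** The case on the other side is substantial, and most of it limits the point without removing it.

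- **The labelled hypothesis is not comparative.** This stands. A reader might infer that an equal fall on both drugs would contradict the trial's hypothesis. It would not contradict the Abstract's sentence, which concerns oestrogen lowering alone. The expectation of doing better than a SERM belongs to the rationale in the Introduction, which argues from tumour incidence and states no prediction for DNA damage on tamoxifen.
- **There is no formal rule.** This also stands. The sentence is an interpretation of an exploratory endpoint in a descriptive study. It still attaches a conclusion to the readout, and the Introduction says the results may provide evidence for further studies.
- **The contrast is already planned.** A reader might infer that the trial ignores the drug-versus-drug comparison. The Comparisons section does not support that, because all three time points are compared within each woman. What is missing is its role in the conclusion. This is not merely detail left to an analysis plan: the article states the inference, and states it without the control.
- **Other mechanism checks exist.** The Introduction ties mechanistic support to damage falling through reduced circulating oestrogen. Table 1 includes metabolite levels and their relation to DNA damage, and Ki67 is stained. These checks help. But damage and metabolites falling together during one course does not separate oestrogen lowering from something else that changes over the same weeks.
- **The drug contrast is not a clean test.** This stands and shapes the fix. Goserelin also lowers progesterone, as the Introduction and Laboratory analysis say, so a larger fall would not isolate oestrogen. No biopsy follows the 4-week washout, so carryover could make the courses look alike. An imprecise null from 12 women cannot refute the mechanism.

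One could also set the 81% to over 99.9% figures against 5%. That mixes two criteria and exaggerates the gap; the comparisons must be made within one criterion.

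**Conclusion.** The point holds in a limited form. As written, the Laboratory analysis inference counts a fall on goserelin/anastrozole as support whatever happens on tamoxifen, so a fall common to both courses would be read as favouring oestrogen suppression. With an equal fall of 0.5 SD, for example, that reading follows 96% of the time on direction alone, against 50% for the drug contrast, or about 49% against 5% with a t bound. These figures rest on assumed values of d, an approximately normal mean, and criteria that the protocol does not itself state. They show the direction and rough size of the problem, not an operating characteristic of the plan. The primary endpoints (consent and compliance) and the participants' treatment are unaffected; only the exploratory mechanistic conclusion is.

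**What to change.** In the Comparisons and Laboratory analysis sections:

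1. Report, as description, the within-woman difference in DNA damage (goserelin/anastrozole minus tamoxifen), averaged over the two sequence groups with a 95% interval and also shown by sequence. Place it beside change from baseline, which stays.
2. Reword the inference so that a fall on goserelin/anastrozole is read as specific to oestrogen suppression only if it exceeds the fall on tamoxifen.
3. State that similar falls on both will be reported as not distinguishing the oestrogen-lowering mechanism from shared or time effects, and will not be taken as refuting it.

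The cost is a few sentences and one paired estimate from samples already planned; no formal test or sample size calculation is needed. The limits should be stated with it:
- The interval will be wide. Treating the 12 differences as one sample, its half-width is about 2.201/√12 = 0.64 SD of the within-woman difference.
- Carryover is possible and cannot be checked, because no biopsy follows the washout.
- Goserelin suppresses progesterone at the same time, so a difference between drugs would not by itself isolate oestrogen.

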### Patient and public involvement

BRCA1 and BRCA2 mutation carriers were involved throughout the design process via the Northern Ireland BRCA mutation carrier support group, BRCA Link NI. The study design was finalised with input from a BRCA patient advocate focus group, where the consensus was that inclusion of an active control treatment was more acceptable than placebo. Women within the group had experienced tamoxifen therapy as part of cancer treatment and deemed potential side effects acceptable in the context of risk reduction. The BRCA mutation carrier cohort in Northern Ireland is overwhelmingly enthusiastic about chemoprevention clinical trials, resulting in a highly motivated patient group keen to contribute to future solutions to BRCA-related breast cancer risk. In keeping with this, the trial management group (TMG) for this study includes a BRCA1 mutation carrier.

